#### Implementation outcomes

Implementation measures are organised using the taxonomy of Proctor and colleagues, who described eight outcome measures for implementation research: acceptability, adoption, appropriateness, costs, feasibility, fidelity, penetration and sustainability.^37^ The current study includes measures within the first six of these outcome domains, acknowledging that the timelines planned for the current trial are likely to be insufficient to obtain a robust assessment of penetration and sustainability. These outcomes will be addressed in future studies.

Adoption outcomes will evaluate whether ‘action steps’ of the model have been implemented: targeted strategies to reduce the backlog of waiting patients, protected capacity for new patients based on demand and changes to models of care to enhance flow. Descriptions of backlog strategies and model of care changes will be obtained through staff focus groups and interviews with patients. The ratio of the number of new patients in the template to referrals received in the pre- and post-implementation periods will be used to determine whether clinics protected capacity to align with predicted demand.

Fidelity of the STAT model will be evaluated by measuring how well these action steps were completed. The outcomes of the backlog reduction process will be described using audit data (including the number of patients removed from this list and reasons why and the number scheduled for care). The average number of new referrals accepted and booked into appointments each week will be used to determine how well the clinics are able to align supply and demand in the pre- and post-implementation periods. Outcomes indicative of changes to models of care delivery at each cluster will be compared pre- and post-intervention, including: mode of care delivery (telehealth/face to face, type of practitioner), appointment outcomes (proportion discharged or booked for review), failure to attend rates, clinical patient contacts outside clinic times (eg, telephone follow-up, calls seeking advice) and the ratio of new to review patients in clinic schedules.

Acceptability, feasibility and appropriateness will be evaluated using qualitative data from staff and patients. Staff perspectives will be sought during the pre-implementation and implementation periods (perceptions of current state, views about the intervention and challenges/enablers for implementation) as well as 6 months after the commencement of the post-implementation period (perceived success or failure of the intervention, impact on patient care, staff workloads and job satisfaction and reflections on feasibility and appropriateness of the STAT model for specialist clinics). Patient perspectives of the clinic service will be sought from samples of patients who attend during the pre- and post-implementation periods.

The total cost of implementation will be considered in two parts: (i) Cost of initial backlog reduction (auditing and short-term additional supply) per patient removed from the waiting list and (ii) total cost of clinic operations during the pre- and post-implementation periods. The cost-effectiveness of the STAT programme will determine the incremental cost per percentage of urgent referrals seen within 30 days and routine referrals seen within 90 days, comparing usual care conditions to intervention conditions. Individual patient health service utilisation cost (outpatient services, emergency presentations and health service admissions) will be collected for the 6 months prior to their first clinic appointment and the first 6 months following this appointment, for patients under usual care conditions and for patients under intervention conditions (estimated n=800).

Outcome measures across all aspects of the trial are summarised in table 3.

**Table 3 T3:** Summary of outcome measures and data sources

	Routinely collected data	Consumer interviews	Staff focus groups	Prospective audits

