#### Health economics data

During the 27-month study period, data for the cost of implementation analysis will be obtained from the following sources: (i) data extracts from clinic administrative and waiting list databases, (ii) audit of patient medical records and (iii) verbal reports obtained from clinic leaders through direct approach and semi-structured interviews. This costing data will be prospectively collected using a customised Excel spreadsheet at the end of each 3-month period (online supplemental file A details the data fields). The spreadsheet will capture 6-month pre-implementation, 6-month implementation and 6-month post-implementation of the STAT model (see figure 1). Cost-effectiveness analysis will include the cost of implementation data, as well as individual participant health service utilisation data, to determine the cost and tracking of patient waiting times to determine the effect.

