### Outcome measures

#### Effectiveness outcomes

Quantitative outcomes will be obtained from routinely collected healthcare data and auditing of health service processes. The primary outcome measure for effectiveness will be waiting, measured as time from initial referral to first appointment and the number of people on the waiting list (measured weekly). Secondary outcomes include the number of emergency department presentations and days admitted to the health service during the 6 months prior to and following the first clinic assessment to determine whether there is a relationship between improved specialist clinic access and other health service utilisation (outpatient services, emergency presentations and health service admissions). These data will be collected for a subgroup of patients attending the clinic for the first time within two of the pre- and post-implementation time blocks (darker shades in figure 1). Factors that may be covariates that impact on waiting times will also be recorded (demographic data, diagnosis and referral source).

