**Implementation outcomes**				
**Adoption**				
Evidence of targeted backlog reduction activity				
Strategies implemented			✓	
Evidence of protected capacity for new patients				
Number of weekly appointments scheduled for new and review patients	✓			
Evidence of changes to model of care				
Staff perceptions of service changes			✓	
Patient experience of services		✓		

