**Fidelity**				
Descriptive analysis of backlog reduction activity				
Number of patients removed from list				✓
Reasons for removal (appointment previously provided, service not needed, unable to contact)				✓
Number of patients scheduled for care				✓
Ratio of expected demand to new patient appointments booked	✓			
Indicators of change in care delivery				
Mode of delivery (face to face, telehealth)	✓			
Number of appointments scheduled by professional type (medical, nurse, allied health)				
Appointment outcomes (proportion rebooked/discharged)	✓			
Attendance (expressed as proportion failed to attend)	✓			
Ratio of new to review patients scheduled	✓			
Contacts with clinic staff outside of the allocated clinic appointments (eg, telephone advice and follow-up)				✓

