### Sample size

A minimum average of 400 referrals is expected to be received for each included specialty annually (100 per quarter), resulting in at least 700 patients across the pre- and post-implementation periods for each cluster (minimum total sample, n=5600). With four steps and eight clusters (two clusters per step), this stepped wedge design will be well powered to detect even small-to-moderate effect sizes. For a mean difference of 0.25 SD in waiting time and a conservative ICC of 0.1, with at least 60 referrals per cluster per 3-month time period (which is less than the pro-rata expected number annually), this design is powered at approximately 90% to sufficiently detect a difference at a 5% level of significance.^38
39^ Again, under conservative assumptions, power for detecting significant differences for our secondary outcomes (eg, an increase in the proportion of urgent patients seen within 30 days from 80 to 90%) exceeds 90%. Compared with our findings from STAT implementation in community outpatient services,^27^ our power and sample size assumptions are chosen conservatively to more than compensate for additional heterogeneity or other differences in the specialised clinic setting.

The sample size for quantitative implementation outcomes is based on the duration of the intervention and length of the waiting lists of the included services. The sample size for the qualitative analysis is considered feasible and expected to be sufficient to reach information power.

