#### Implementation

Quantitative implementation outcomes, including the outcome of the waiting list audits, the ratio of demand to clinic capacity for new patients and indicators of change in patient flow, will be analysed descriptively. Qualitative data generated from staff will be mapped deductively to the domains of the Consolidated Framework for Implementation Research (CFIR). Rating rules for the CFIR and a cross-comparison analysis will be used to compare the experiences of different clinic teams.^42^ This method of analysis allows each comment made by participants to be coded in relation to its relevance to a subdomain of the CFIR and rated as ± according to whether the comment suggests a positive or negative influence of the factor on implementation.

Qualitative data generated from patients will be analysed using a thematic matrix analysis.^43^ Initially, the interview transcripts will be coded inductively line by line, then codes will be used to identify themes and subthemes. These themes will then be organised into a matrix to compare perceptions of patients who attended the clinic during the pre-implementation period and those who attended during the post-implementation period.

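### Protected new-patient capacity could come at the cost of review care, but review appointments and discharge get only a raw before-and-after description that cannot be attributed to STAT

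*Protocol article*

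**What the plan says.** Under Intervention and implementation strategy, step 4 of STAT protects clinic capacity for new patients in line with demand. Short-term extra supply, a part-time coordinator and the step 5 flow strategies accompany it.

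The effectiveness outcomes (Effectiveness outcomes; Table 3) are time from referral to first appointment, proportion seen within thresholds, number on the waiting list, and health service use. On health service use the article says: "These data will be collected for a subgroup of patients attending the clinic for the first time".

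Review activity appears only among the implementation outcomes. Table 3 lists "Number of weekly appointments scheduled for new and review patients" under Adoption and "Appointment outcomes (proportion rebooked/discharged" under Fidelity. The text on fidelity adds "the ratio of new to review patients in clinic schedules". The stated contrast is: "Outcomes indicative of changes to models of care delivery at each cluster will be compared pre- and post-intervention". Under Analysis, Implementation, the quantitative implementation outcomes, including "indicators of change in patient flow, will be analysed descriptively".

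The mixed models with a time-point factor, and the binomial and negative binomial versions for proportions and counts, are set out under Analysis, Effectiveness.

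**The concern.** If total clinic capacity does not grow, slots reserved for new patients come from somewhere, and the established review caseload is the obvious place. The offsets named in the protocol may prevent this, so it is a possibility and not a prediction.

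The trial already collects data that would show a change in review volume or discharge. However, it plans to read them as before against after, without adjustment for calendar time. In a stepped wedge every cluster moves from control to intervention in the same direction in time, so averaging over clusters does not cancel a trend common to all of them. The staggered, randomised start is what allows such a trend to be separated from the intervention, and the planned description of these measures does not use it.

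At stake is a report of shorter waits for new patients that cannot say whether review capacity or discharge changed because of STAT. The Design section says the findings are meant for providers deciding on services and funding, and those readers would want both.

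**Working it through.** **Schedule.** Inputs from Design: start 31 March 2025, end 27 June 2027, 6 months of control data, two clusters per step, a step every 3 months, 6 months of implementation per cluster. The span is 819 days = 117 weeks = 9 quarters of 13 weeks. For step k = 1 to 4, pre is quarters 1 to k+1, implementation is quarters k+2 to k+3, and post is quarters k+4 to 9.

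**The article's own figure.** Pre plus post is 9 - 2 = 7 quarters per cluster. At 100 referrals per quarter that is 700, which matches Sample size ("resulting in at least 700 patients across the pre- and post-implementation periods for each cluster"); 8 x 700 = 5600 also matches.

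**Distance between pre and post.**
- Edge to edge: 6 months, the implementation period.
- Midpoint to midpoint, all quarters: step 1, 19.5 - 3; step 2, 21 - 4.5; step 3, 22.5 - 6; step 4, 24 - 7.5. Each is 16.5 months, or 5.5 quarters.
- Midpoint to midpoint, 6 months on each side of implementation: 3 + 6 + 3 = 12 months, or 4 quarters, in every step. These lengths are those of the costing data ("The spreadsheet will capture 6-month pre-implementation, 6-month implementation and 6-month post-implementation of the STAT model"), read here as adjacent windows.

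The sections on implementation outcomes and their analysis do not fix the window, so both are shown.

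**What drift alone would show.** The article gives no drift in review activity. Assume drift g per quarter common to all clusters and no STAT effect. The apparent change is (1+g)^4 - 1 or (1+g)^5.5 - 1.

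| Drift per quarter | 12-month midpoints | 16.5-month midpoints |
|---|---|---|
| 1% down / up | -3.9% / +4.1% | -5.4% / +5.6% |
| 2% down / up | -7.8% / +8.2% | -10.5% / +11.5% |
| 3% down / up | -11.5% / +12.6% | -15.4% / +17.7% |

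**What a time-adjusted model could deliver.** Clusters in pre / implementation / post are 4/4/0 in quarter 4, 2/4/2 in quarter 5 and 0/4/4 in quarter 6. Only quarter 5 holds both pre and post clusters. Take log counts in 8 x 9 = 72 cells, with cluster effects, quarter effects, an implementation level and one post level (18 parameters, so 54 residual df). With independent cell errors, the SE of the post term is 0.781 x the cluster-quarter SD. Leaving out the implementation quarters raises it to 1.09 x SD.

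The SD is also assumed. The 95% half-width on the log scale is 0.078 (54 df) to 0.092 (7 df) at SD 5%, and 0.157 to 0.185 at SD 10%. Count noise alone is 1/sqrt(400) = 5% at 400 appointments, so SD 5% needs at least 400 review appointments per cluster-quarter. Review volume is not given.

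**When the raw contrast does better.** Its SE is 0.283 x SD (all quarters) or 0.354 x SD (6-month windows), but it carries the drift as bias. Root mean squared errors are equal at a drift of sqrt(0.781^2 - 0.283^2)/5.5 = 0.132 x SD or sqrt(0.781^2 - 0.354^2)/4 = 0.174 x SD per quarter. That is 0.66% or 0.87% at SD 5%, and 1.3% or 1.7% at SD 10%. Below these values the raw contrast is closer to the truth on average, though it still cannot show that drift was small.

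**The case against.** The strongest reply is that nothing here is an error. The stated effectiveness aim is waiting lists and waiting times, and describing fidelity data descriptively is coherent. This stands, and it limits the point to an improvement. It is still more than detail left to an analysis plan, because the article itself fixes both the contrast and the type of analysis.

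Second, review care is not wholly unmodelled. Outpatient use in the 6 months after the first visit is a secondary outcome and falls under the generalised mixed models. It may capture early review visits of first attenders, although the article does not say whether same-clinic reviews count. It does not reach the established caseload.

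Third, other safeguards exist. Staff focus groups ask about the effect on patient care, contacts outside clinic are audited, and the monitoring committee looks for unintended consequences at clusters A and B. These help interpretation, but none gives a time-adjusted estimate for the established review caseload across the eight clusters. A descriptive display by calendar quarter and cluster is not excluded and would help a reader see drift.

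Fourth, the remedy is imprecise. At SD 5% its half-width of 8-9% exceeds the error that 1% drift produces. This stands, and it is why the model should be added to the description and not replace it.

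Finally, fewer reviews or more discharges may be what STAT intends, since clinicians decide on later care with need and capacity in mind. This also stands: the estimate cannot tell intended discharge from harmful displacement.

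**Conclusion.** The point holds as a cheap improvement. As planned, the trial can describe changes in review appointments and discharge but cannot attribute them to STAT, because post follows pre by 12 or 16.5 months between midpoints in every cluster. The illustrative size, about 4-18%, rests entirely on assumed common drift of 1-3% per quarter. The precision figures rest on an assumed cluster-quarter SD.

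A reader might infer three stronger things that the article does not support:
- That STAT will displace or harm review patients. The article names offsetting measures and contains no data on this.
- That descriptive reporting is itself wrong or undermines the waiting-time result. It suits fidelity measures, and the primary analysis has its own time-point factor.
- That pre and post data lie more than a year apart. The periods are 6 months apart at their edges; the longer figures are distances between midpoints.

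**What to change.** Keep the descriptive fidelity report. Add two supportive balancing outcomes from data already listed in Table 3: weekly review appointments scheduled per cluster, and the proportion of appointments ending in discharge. Fit them with the negative binomial and binomial mixed models already named under Analysis, Effectiveness. Use the time-point factor, implementation quarters as their own level, a single post-implementation term and a small-sample correction. Report 95% CIs as estimates, not tests, beside the waiting-time result, and read the new-to-review ratio together with absolute review counts.

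State the limits in the same place:
- Only drift common to all clusters is removed; specialty-specific drift remains as error.
- Intervals will be wide, and a wide interval does not show absence of displacement.
- If drift is small, the raw contrast has the lower mean squared error.
- The measures show capacity and discharge, not overdue reviews, harm, or whether a fall was intended.

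The cost is a few sentences and two further models on data already collected, with two more secondary estimates to report. No change to the design or the primary analysis is needed.

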23^ Long-term supply-side solutions are often hampered by workforce shortages and lack of funding. Triage systems are often used as a demand management tool but frequently lack reliability and contribute to inefficiencies by directing resources away from frontline care while doing little to solve the underlying problems contributing to the existence of the waiting list in the first place.^24^ Service providers are left with an impression that waiting lists are inevitable and give up on seeking solutions.^25^

However, there are a range of strategies that can be introduced by health services to reduce outpatient waiting times. Examples of principles of successful strategies include balancing supply and demand, improving efficiency of processes and protecting capacity for new patients and role substitution, in which alternative health providers undertake roles otherwise conducted by more specialised professionals.^10
11
13^ These strategies have been used in various combinations, often tailored to local context.^13^ This evidence is supported by consistent findings from a large number of studies, although limited by a predominance of single-group, observational study designs.^13^

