## Method

### Setting

The trial will take place at Eastern Health, a large network of metropolitan services in the eastern suburbs of Melbourne, Australia, providing publicly funded health services to a diverse community of approximately 892 000 people, including a high proportion (32%) of residents born overseas. Eastern Health offers a broad range of services, including emergency care, surgery, maternity, palliative care, mental health, drug and alcohol services, residential care and community health, delivered across three tertiary hospitals, two sub-acute inpatient services, a small community hospital, a day surgery centre and more than 30 community sites. The inclusion of a single health service could be seen as a limitation, but the size of the health network and its operation across multiple sites spanning a diverse geographical catchment provide confidence in the applicability of the findings to a broad range of health settings.

Eastern Health operates a comprehensive network of specialist medical clinics, providing expert care across a broad range of medical disciplines. Patients are typically referred to these clinics by general practitioners, specialists or hospital-based clinicians. Referrals are made electronically, then triaged by clinicians and assigned a priority category. Urgent referrals may be booked directly into appointments, while routine referrals are waitlisted until an appointment becomes available. Waiting times vary from weeks or months to several years.

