### Intervention and implementation strategy

The intervention will consist of a suite of service redesign initiatives based on the STAT model. During the implementation period, staff within each cluster will be trained in the STAT model in workshops of 1–4-hour duration (tailored for teams and individuals according to prior knowledge of STAT and role within the service, with options for flexible delivery), led by investigators [name] and [name]. This training was developed at Eastern Health/La Trobe University and has been delivered to more than 1000 clinicians across Australia from more than 100 services over the past 4 years.^35^

Following training, the clinic staff will be guided through each of five steps of the STAT model: (i) analyse clinic supply and demand data, (ii) model supply and demand at the clinic, (iii) targeted interventions to address the existing backlog (using a comprehensive waiting list audit supplemented by targeted, short-term supply-side interventions), (iv) protect capacity for new patients to align with demand and (v) implement tailored strategies to enhance patient flow. Step 5 will incorporate enhanced clinic coordination, alongside other strategies that could include (but are not limited to) productivity improvements (such as reducing failure-to-attend rates), multi-disciplinary approaches to service delivery and partnerships with patients and primary care (table 1).

**Table 1 T1:** Key WaitLESS intervention activities and corresponding resources

Key activities	Resources provided
**Staff training** in the principles of the STAT model	Four-hour workshop training provided by members of the research team
**STAT Step 1:** Retrospective collection and analysis of clinic data—typical supply and demand over past 2 years	Support from research team/project manager
**STAT Step 2:** Model supply and demand; determine how much capacity needs to be protected for new patients to maintain flow at the rate of demand	Support from research team/project manager
**STAT Step 3**: Address existing backlog. Example activities: Comprehensive waitlist audit: cleaning the list, including checking for errors and calling/messaging patients to determine need Short-term increase in supply Grouping similar patients for targeted interventions	Clerical assistance for auditing Some funding for additional short-term clinic supply
**STAT Step 4:** Redesign clinic templates to align with demand	Support from research team/project manager

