**Effectiveness outcomes**				
Primary outcomes:				
Time from referral to first appointment	✓			
Proportion of patients seen within thresholds	✓			
Number of patients on the waiting list	✓			
Covariates:				
Demographic data	✓			
Referral data	✓			
Secondary outcomes:				
Health service use (outpatient services, emergency presentations and health service admissions)	✓			

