A cost of implementation and cost-effectiveness analysis will be completed from a health service perspective. A priori subgroup analysis of clinic patient types (urgent vs routine) will be completed as part of the economic evaluation. The cost of implementation will include two parts: (1) the cost of initial backlog reduction and (2) the cost of clinic operations. The cost of initial backlog reduction will be calculated by dividing the total cost by the incremental difference in the number of patients on the waitlist at the end of the pre-implementation period and the number of patients on the waitlist at 30-day post-implementation. The total cost of clinic operations will be calculated using quarterly audits throughout the trial to record all usual care costs (usual care staffing, capital and overhead costs) as well as any additional investment associated with the intervention, less the income derived from activity-based funding received by each cluster. A unit cost will be calculated by dividing the total cost for each cluster in each 3-month period by the number of new patients who receive a first appointment with a clinic within that cluster during that time. Each of these costs will be reported as a cost per cluster and as mean costs (with SD) across clinics. Costing at the service level will enable comparative efficiency measures such as the ratio of inputs to service output. The cost of implementation analysis will be presented as an overall cluster cost, as well as a cluster cost for the pre-implementation period and as a cluster cost for the post-implementation period.

To establish the incremental cost-effectiveness ratio (ICER), pre-implementation to post-implementation, cost differences will be divided by the percentage difference of urgent and routine referrals seen within 30 and 90 days, respectively, to determine the cost per 1% increase in the proportion of patients seen within these thresholds. ICERs will be determined by bootstrapping individual cost and effect data 5000 times, and this will be presented as an ICER value with 95% CIs and visually presented on a cost-effectiveness plane.

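### The 30-day urgent and 90-day routine access outcome, and the ICER built on it, depend on a triage category that the masking does not cover and that could shift after implementation

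*Protocol article*

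**What the plan says.** All references are to the protocol article.

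- **Definition.** Under Implementation outcomes, cost-effectiveness is expressed as "the incremental cost per percentage of urgent referrals seen within 30 days and routine referrals seen within 90 days". The Implementation part of the Analysis section divides the cost difference by the change in these percentages, "to determine the cost per 1% increase in the proportion of patients seen within these thresholds".
- **Rank.** Table 3 lists "Proportion of patients seen within thresholds" among the primary effectiveness outcomes. The Sample size section treats the urgent proportion as secondary, and the text under Effectiveness outcomes does not name the threshold proportions as primary.
- **Power example.** The Sample size section states that "power for detecting significant differences for our secondary outcomes" exceeds 90%, and gives as its example "an increase in the proportion of urgent patients seen within 30 days from 80 to 90" per cent.
- **Source of the category.** Under Setting, referrals arrive electronically and are "then triaged by clinicians and assigned a priority category". Urgent ones may go straight to an appointment; routine ones join the waiting list.
- **Who is trained.** Under Intervention and implementation strategy, "staff within each cluster will be trained in the STAT model". Under Inclusion criteria, all staff of a participating specialty, medical staff included, are invited to take part in the reforms.
- **Masking.** Randomisation and masking relies on central, independent collection of referral dates, appointment dates and waiting-list allocation. The priority category is not mentioned.
- **View of triage.** The Introduction says: "Triage systems are often used as a demand management tool but frequently lack reliability".

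**The concern.** A patient counts as seen in time according to a limit chosen by the patient's own category. Someone first seen on day 45 is a failure if urgent and a success if routine. If borderline referrals are labelled urgent less often after implementation, the urgent denominator loses failures and the routine numerator can gain successes, while no appointment moves.

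This needs no misconduct. Under usual care the urgent label can bypass the queue. STAT is meant to book new patients without a waiting list, so once routine waits fall there is less reason to call a borderline referral urgent. The intervention could in this way change the category mix.

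At stake is a labelling shift reported as better access. Where the cost difference is positive, it would also make the cost per percentage point look smaller than it is.

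**Working it through.** **1. The plan's own figure.** The power above 90% for 80% to 90% cannot be reproduced, because the number of urgent referrals per cluster-period is not given. Assume a plain stepped wedge with 8 clusters, 4 steps, 5 periods, a random cluster effect, ICC 0.1, binary variance 0.85 × 0.15 = 0.1275 and power = Φ(0.10/SE − 1.96). Power is then 39.6% with 10 urgent referrals per cluster-period, 65.1% with 20, 81.4% with 30, 90.7% with 40 and 97.9% with 60. With nine quarters and the 6-month implementation periods left out, it is 13.7% with 10, 31.8% with 30 and 55.4% with 60. Below, the example is used only for its two percentages.

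**2. Effect of relabelling on the urgent proportion, waits held fixed.** Inputs:

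- 80% and 90%, from the Sample size section;
- x, the share of urgent referrals moved to routine (assumed);
- q, the share of those moved that would have missed 30 days (assumed).

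The urgent proportion after the move is (0.80 − x(1 − q)) / (1 − x). Setting it to 0.90 gives x = 0.10 / (q − 0.10).

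| q | x needed for 90% | urgent proportion if x = 11.1% |
|---|---|---|
| 1.0 | 0.10/0.90 = 11.1% | 90.0% |
| 0.8 | 0.10/0.70 = 14.3% | not computed |
| 0.6 | 0.10/0.50 = 20.0% | 85.0% |
| 0.5 | 0.10/0.40 = 25.0% | 83.75% |
| 0.2 | not attainable | 80.0% |

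At q = 1 the moved referrals are 0.111/0.20 = 55.6% of all late urgent referrals. At q = 0.2, the overall late rate, the proportion is (0.80 − 0.80x)/(1 − x) = 0.80 for any x below 1.

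**3. Both proportions together.** Assumed counts: 40 urgent with 32 in time, and 60 routine with 30 in time. Move 4 late urgent patients who were all seen by day 90.

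- Urgent: 32/40 = 80% becomes 32/36 = 88.9%.
- Routine: 30/60 = 50% becomes 34/64 = 53.1%.
- Pooled, each patient judged by their own limit: 62/100 becomes 66/100.
- All referrals seen within 30 days, and within 90 days, regardless of category: unchanged, because no wait has changed.

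If instead 4 of the 40 are moved at random (3.2 of them in time), urgent stays at 28.8/36 = 80%, routine becomes at least 33.2/64 = 51.9%, and pooled is at least 28.8 + 33.2 = 62 of 100. If the ICER wording is read as pooled, a move from urgent to routine at fixed waits can never lower it: anyone seen within 30 days is also within 90, and everyone seen on days 31 to 90 becomes a success.

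**4. The routine proportion can also fall.** Take 100 urgent and 100 routine referrals, routine at 50%, and move 11.1. Routine becomes 45.0%, 50.0% or 55.0% if none, half or all of those moved are seen by day 90.

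**The case against.** **Selectivity.** Setting describes triage before booking, so the category is given before anyone knows whether the patient will be late. A reader might infer that relabelling about one urgent referral in nine is enough to produce the whole target effect. That is only the minimum, and it requires picking out over half of the late urgent referrals without error. This objection stands for the urgent proportion. It does not dispose of the routine or pooled figures, which can rise under random relabelling (step 3).

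**Fixed waits.** Since urgent referrals may be booked directly and routine ones are waitlisted, category itself influences the wait. A referral moved to routine might wait longer and fail its 90-day limit. This stands: the fixed-wait arithmetic is an illustration, not a forecast.

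**Who triages.** A reader might infer that the trained staff are the people who assign the category. The article says only that clinicians do so. It is a reasonable inference, because all specialty staff are invited into the reforms, but it is not stated. Nor does any of the five STAT steps mention changing the urgency criteria.

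**Unreliable triage.** The Introduction's remark is general background. Unreliability is noise and does not show a shift after implementation. This stands; the remark shows only that the label leaves room for judgement.

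**Main outcomes.** A reader might infer that the lead effectiveness result is compromised. It is not: neither the wait from referral to first appointment nor waiting-list size is defined by category. A purely cosmetic threshold gain would sit beside an unchanged waiting time, which limits the harm. The ICER, however, uses the thresholds and not the waiting time. The planned urgent-versus-routine economic subgroups are split by the same category, so they give no protection.

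**Conclusion.** The point holds in a limited form. The threshold proportions and the ICER effect take both time limit and denominator from a post-randomisation category outside the masking argument, so a shift in category mix could pass as earlier access. With waits fixed, reproducing 80% to 90% takes 11.1% of urgent referrals at the least, 14.3% to 25% if 80% to 50% of those moved would have been late, and cannot happen if relabelling is unrelated to lateness.

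The documents do not show that such a shift will occur, how large it would be or in which direction; a shift from routine to urgent would bias the other way. The routine counts, the values of x and q, and the fixed waits are assumptions. The conclusion that the outcome is exposed does not depend on them. It does rest on unblinded staff being able to influence the category, which is inferred.

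**What to change.** - Keep the category-specific proportions and the ICER based on them.
- Add the proportion of all accepted referrals seen within 30 days, and the proportion seen within 90 days, regardless of category. Make this a pre-specified analysis of the threshold outcome and a sensitivity analysis for the ICER.
- Report the urgent share of referrals by cluster and quarter next to these results.
- State in advance that a category-specific gain is not interpreted as improved access where the urgent share has shifted and the category-free result does not agree.

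Using the category recorded at first triage would stop later recoding. It would not be enough alone, since first triage after implementation may still be done by unblinded staff.

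The cost is outcome wording and one additional set of results, from dates and categories the stated outcomes already need. The downside is that all-referral proportions do not match the category-specific targets and could hide worse urgent access behind routine gains, which is why they are added and do not replace the existing measures.
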